### 3.9. Cost-Effectiveness Analysis

The intervention cost will be calculated by considering average times (including both patient contact and non-contact) for the pharmacist at each consultation (baseline, at 6 months, at 12 months, and any additional consultations). Participant attendance rates, recorded by the pharmacist delivering the intervention, will be combined with the estimated cost per consultation, allowing for the total cost of all consultations to be calculated for each participant. Pharmacists will receive proper training to convey the intervention using a tablet and other equipment (e.g., booklet, BP record book) from each participating pharmacy. All of these items will be documented along with their associated costs, including pharmacist time (cost calculated as above), equipment costs, and consumables for blood pressure measurement. Pharmacist training costs will also be measured. To calculate the per-patient total intervention costs, all of the above-mentioned costs will be equally divided among all intervention group participants and then added to the aforementioned per-patient total consultation cost. The cost of each activity will be valued using standard rates. Finally, the cost per unit (mmHg) of blood pressure reduction and/or cost per HRQoL gain will also be measured.

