### 3.6. Intervention

This project will consist of three phases: baseline survey with first-time intervention implementation; second intervention at 6 months; and third, endline survey at 12 months. The details of the intervention content are mentioned in Table 1. As part of the intervention within the randomized selected groups, the CP will conduct two 15–30 min sessions throughout the intervention period, once at the baseline or first visit (T0) and once at the sixth month (T1). Patients will attend the two sessions at the pharmacies where they collect their prescription medication. Face-to-face counseling sessions will be held about hypertension and its management, including lifestyle changes and drug compliance. Patients will be able to view the educational material in the pharmacy via a tablet since audio–visual presentations make learning easier. The detailed training material and handbook are presented as Supplemental Files S1 and S2. To maintain adherence to intervention, the intervention group will receive phone call intervention at 3 months and 6 months. The patient will be reminded every time about their subsequent visits via phone calls/short message services (SMS). Patients’ BP will be monitored routinely during each session, and information regarding medication and complications will also be obtained. This intervention will be low in cost, aligned with the current CP workflow, and will not require any significant changes in the existing system. Both interventions will be conducted by the same pharmacist to ensure consistency. Furthermore, CPs in the intervention group will receive a checklist of items and a counseling protocol to prepare them for what they need to do during patient visits. A pilot study was conducted in two pharmacies in Bangladesh before starting the study in order to optimize the intervention steps and materials. Nevertheless, there are no restrictions on how many times the patient may meet the pharmacists outside of these ‘core’ consultations. In this case, the patient will decide with the pharmacist according to needs, and it is suggested that this coincides with the monthly collection of prescriptions.

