In the control group, routine pharmacy services and counseling will be provided without interference during all pharmacy visits, as per each country’s pharmacy practice guidelines, and they will serve as a comparator group to determine the impact of the intervention implementation. Assessments will be completed at the same time points as those in the intervention group.

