Additional data will be collected by enumerators to enable the calculation of the QRisk2 score, including the following:Blood pressure (lowest of two measurements used);Fasting blood glucose level;Weight and height;Smoking status (options aligned with QRisk2).

For the economic evaluation, all costs related to pharmacy-based intervention will be collected including patient counseling and education time and training, telephone and material costs, cost of care at the hospital (for complicated cases requiring visits to physicians and admission), and other administrative costs.

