### 3.13. Statistical Analysis

All outcomes will be analyzed using the intention-to-treat principle. Descriptive statistics will be used to present baseline characteristics and outcome variables. Percentages and frequencies will be used for categorical variables, and means and standard deviations will be used for continuous variables. Baseline characteristics between the two arms will be compared with chi-square or Fisher’s exact test, as appropriate. A multilevel mixed model will be used to compare the differential changes in each outcome across the time points (T1, T3, and T5) to measure the primary and secondary outcomes. We will analyze group changes (with individual pharmacies treated as a random effect) using multivariable mixed linear and non-linear regression for normally and non-normally distributed data to account for the cluster randomization effects. Point estimates from cluster-adjusted models will be reported with 95% confidence intervals. Additionally, subgroup analysis will stratify data based on hypertension-related complications and the number of associated medications to estimate the effect of the interventions. For all two-tailed statistical tests, *p*-value < 0.05 will be considered statistically significant. We will perform all statistical analyses using R (version 4.1) and Stata software (version 17.0).

A cost-effectiveness analysis will be performed on the average total cost incurred in both arms, and incremental cost-effectiveness ratios expressed as incremental cost per (1) 1, 5, or 10 unit (mmHg) decrease in blood pressure; (2) one hospital admission reduced; (3) 1 day of hospital stay reduced over the previous 6 months among the survivors; and (4) HRQoL using data from EQ-5D-5L and mortality. We will calculate all cost data in US dollars, using the non-subsidized cost as of the study’s commencement.

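### Pharmacist contact, including additional visits, is costed in the intervention arm only, so incremental cost is biased upward to the extent that those visits replace or include usual-care counselling

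*Protocol article*

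**What the plan says.** Section 3.9 (Cost-Effectiveness Analysis) sets out how pharmacist time is priced. Average contact and non-contact times are taken at four kinds of consultation: "baseline, at 6 months, at 12 months, and any additional consultations". Attendance is the intervention pharmacist's own record: "Participant attendance rates, recorded by the pharmacist delivering the intervention, will be combined with the estimated cost per consultation". Training, equipment and similar items are then spread over one arm: "all of the above-mentioned costs will be equally divided among all intervention group participants".

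Section 3.6 (Intervention) plans two core sessions, at baseline and month 6. It sets no limit on further meetings with the pharmacist, and of these it says that "it is suggested that this coincides with the monthly collection of prescriptions". For the control arm the same section states that "routine pharmacy services and counseling will be provided without interference during all pharmacy visits".

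Section 3.13 (Statistical Analysis) bases the cost-effectiveness analysis on "the average total cost incurred in both arms". It forms incremental ratios per mmHg, per admission avoided, per hospital day avoided and per HRQoL gain.

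Section 3.7 (Data Collection) describes the economic data in terms of the intervention: "all costs related to pharmacy-based intervention will be collected including patient counseling and education time and training", together with telephone, material, hospital and administrative costs.

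**The concern.** Counselling by a pharmacist at a pharmacy visit occurs in both arms. In the intervention arm it is timed, counted and priced whenever it is recorded as an additional consultation. In the control arm the article describes no rule that prices it and no patient-level record from which it could be priced later.

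The comparison of arm totals in 3.13 needs the net difference in pharmacist contact. The costing rule in 3.9 supplies the gross amount in one arm. All four ratios share the same numerator, so an error in incremental cost reaches each of them. Incremental cost per HRQoL gained is a listed secondary outcome in 3.8, and cost-effectiveness is part of the stated aim. Control contact that is not recorded during follow-up is hard to reconstruct afterwards.

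**Working it through.** The article states no unit cost, contact rate or cost-effectiveness ratio, so there is no figure of the plan's own to reproduce on this point. The check has three steps.

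**1. Is control-arm pharmacist contact captured elsewhere?**

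| Place | What it collects | Gives pharmacist time per control patient? |
|---|---|---|
| 3.7, clinical factors | Hospitalisation, days in hospital, doctor visits | No |
| 3.7, organisational information | Monthly visits by hypertensive patients, per pharmacy, in either arm | No: a pharmacy total, without time, cost or link to participants |
| 3.8, service use | Physician visits, admissions, death | No |
| Table 2 | Direct and indirect treatment cost, both groups, months 0, 6 and 12 | Not said to include pharmacist time |

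Section 3.11 also refers to pharmacist counselling in either group, so control contact is expected to occur.

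**2. Direction of the error**

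Per patient, let:

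- F = training and equipment cost
- k = number of core sessions, at cost c each
- A = costed additional consultations in the intervention arm
- U = routine pharmacist contacts of a control patient
- w = cost of one non-core contact
- D = difference in other care costs
- p = share of U that, in the intervention arm, is replaced by or recorded within the costed additional consultations (0 to 1). The rest of the routine contact is taken to be the same in both arms.

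Then:

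- As described: F + c·k + w·A + D
- Like for like: F + c·k + w·A + w·(1 − p)·U − w·U + D = F + c·k + w·(A − p·U) + D
- Excess: w·p·U

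The excess is zero if the additional consultations come wholly on top of usual care (p = 0) or if controls have no costed contact (U = 0). Its upper limit is w·U, the full cost of control contact.

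**3. Illustrative size**

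Every value here is assumed. The cost of one core session is the unit (c = 1), with F = 1, D = 0, A = U, p = 1 and w from 0.1 to 1.0.

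| A = U | k = 2, ratio described / like for like | k = 3 |
|---|---|---|
| 0 | 3.0/3.0 = 1.00 | 4.0/4.0 = 1.00 |
| 4 | 3.4/3.0 = 1.13 to 7.0/3.0 = 2.33 | 4.4/4.0 = 1.10 to 8.0/4.0 = 2.00 |
| 10 | 4.0/3.0 = 1.33 to 13.0/3.0 = 4.33 | 5.0/4.0 = 1.25 to 14.0/4.0 = 3.50 |

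The k = 3 column counts the 12-month consultation that 3.9 costs. With only half the routine contact overlapping (p = 0.5, k = 2, A = U = 10, w = 0.25), the figures are 3 + 2.5 = 5.5 against 5.5 − 1.25 = 4.25, a ratio of 1.29.

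The sign can also change. With k = 2, A = U = 10, w = 0.25, p = 1 and a care-cost saving of 4 units, the described incremental cost is 2 + 1 + 2.5 − 4 = +1.5. The like-for-like value is 2 + 1 + 0 − 4 = −1.0. A cost saving would then be reported as a net cost.

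**The case against.** The strongest reply is that 3.9 prices the intervention and was never meant to be the rule for each arm's total. That rule is in 3.13, which names both arms, and a journal article may leave unit costing of usual care to a fuller plan. Nowhere does the article say that control contact is priced at zero. In addition, extra meetings agreed according to need may be true additions made at an existing visit, and then it is correct to charge them to one arm only.

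Much of this stands, and it limits the point in three ways.

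- A reader might infer that no pharmacist contact at all is measured in controls. The documents do not support that: 3.7 counts visits per pharmacy without restriction by arm, and Table 2 collects treatment costs in both groups. What is not described is patient-level pharmacist time or cost for controls.
- A reader might infer that every cost-effectiveness ratio is overstated. That requires overlap with usual care, a positive effect and no change in the sign of incremental cost.
- A reader might put a percentage on the excess by assuming a number of monthly visits and minutes per visit. Those inputs are not in the documents, and such a figure would cover pharmacist minutes only, not training, equipment, telephone or hospital costs.

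The reply does not remove the mismatch. The article does fix a rule, it includes additional consultations in that rule, and it suggests an occasion for them on which controls may also be counselled. Naming both arms in 3.13 states the aim without supplying the control-arm input.

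**Conclusion.** The point holds in conditional form. The costing rule in 3.9 charges additional pharmacist contact gross to the intervention arm, and the article describes no matching patient-level item for controls. If the rule is applied as written, incremental cost is biased upward by w·p·U per patient. The direction follows from the rule, given some overlap with usual care and otherwise equal routine contact in the two arms. The size does not follow, because w, p and U are all absent from the documents; the ratios of 1.00 to 4.33 only show how much depends on them. The consequence may be higher ratios or a concealed cost saving. It should be corrected before follow-up data are collected.

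A related inconsistency bears on the same total: 3.9 costs a 12-month consultation, while 3.6 plans two sessions and Table 2 shows no intervention component at month 12.

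**What to change.** In 3.9, state that non-core pharmacist contact is costed the same way in both arms. Ask every patient, in the existing month 6 and month 12 interviews, how many pharmacist consultations they had since the last survey and how long these usually took. Apply one unit cost to both arms, so that only the net difference enters incremental cost. Say in 3.13 that total cost in each arm includes this item. The per-pharmacy visit counts in 3.7 can serve as a rough plausibility check.

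The cost is one or two extra questions and some recall error.

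Additional consultations should not simply be dropped from the intervention arm. Section 3.6 expressly allows them, and where they are truly extra, leaving them out would understate the cost of the intervention.

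Reconcile the 12-month consultation in 3.9 with the sessions listed in 3.6 and Table 2, so that the number of costed core contacts is unambiguous. This needs only wording.

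### Read literally, the costing rule in section 3.9 counts pharmacist consultation time twice, once in the equally shared pool and once per patient

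*Protocol article*

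**What the plan says.** Section 3.9 (Cost-Effectiveness Analysis) sets out the intervention cost in this order:

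1. Consultation cost is based on "average times (including both patient contact and non-contact) for the pharmacist at each consultation". The consultations named are those at baseline, 6 months and 12 months, plus any additional ones. Attendance is combined with a cost per consultation, "allowing for the total cost of all consultations to be calculated for each participant".
2. The text turns to training and equipment: "Pharmacists will receive proper training to convey the intervention using a tablet and other equipment (e.g., booklet, BP record book".
3. These items are to be documented with their costs, "including pharmacist time (cost calculated as above), equipment costs, and consumables for blood pressure measurement".
4. A separate sentence follows: "Pharmacist training costs will also be measured".
5. The sum: "all of the above-mentioned costs will be equally divided among all intervention group participants and then added to the aforementioned per-patient total consultation cost".

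Section 3.13 (Statistical Analysis) then states: "A cost-effectiveness analysis will be performed on the average total cost incurred in both arms". The incremental ratios listed there (per mmHg, per admission, per hospital day, per unit of HRQoL) all draw on that cost.

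**The concern.** Step 5 adds two quantities: an equal share of a pool, and the patient's own consultation cost. The pool is everything mentioned before, and step 3 names pharmacist time as part of it, costed by the earlier calculation. The only earlier calculation of pharmacist time is the consultation cost in step 1. Nothing in the section takes consultation time out of the pool before the consultation cost is added.

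Cost-effectiveness is part of the stated aim (section 2) and of the objectives (section 2.2). If an analyst follows the rule as worded, the extra cost falls only on the intervention arm, so the error always runs against the intervention. Section 3.6 describes the programme as low in cost and built around counselling. Consultation time may therefore be a material share of its cost, though the article gives no figure.

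**Working it through.** **Inputs.** The article states no monetary figure, so there is no result of the plan's own to reproduce. The check is algebra on the section 3.9 rule, with assumed shares.

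- n: number of intervention participants.
- C: mean consultation cost per intervention patient (step 1 of the rule); no value given.
- F: per-patient share of all non-consultation intervention costs; no value given.
- s = C/(C + F): consultation share of intervention cost; assumed.
- H: between-arm difference per patient in all other costs, such as hospital care, which section 3.7 says will be collected; assumed.

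**Intervention cost per patient**

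- Literal rule: the pool is nC + nF. The mean is (nC + nF)/n + C = 2C + F.
- Consultation time counted once: the pool is nF. The mean is nF/n + C = C + F.
- Excess: (2C + F) − (C + F) = C.
- Factor: (2C + F)/(C + F) = 1 + s.

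| Assumed s | Factor on intervention cost |
|---|---|
| 0.10 | 1.10 |
| 0.25 | 1.25 |
| 0.50 | 1.50 |
| 0.75 | 1.75 |
| 0.90 | 1.90 |

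**Numerator of the ratios.** The numerator is the difference in average total cost between arms: C + F + H with a single count, 2C + F + H on the literal rule. The excess is C in both cases, but its proportional size depends on H. Set the single-count intervention cost C + F to 1 and s to 0.5, so C = 0.5:

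| Assumed H | Single count (1 + H) | Literal rule (1.5 + H) | Factor |
|---|---|---|---|
| +2.0 | 3.0 | 3.5 | 1.17 |
| +0.5 | 1.5 | 2.0 | 1.33 |
| 0 | 1.0 | 1.5 | 1.50 |
| −0.5 | 0.5 | 1.0 | 2.00 |
| −1.2 | −0.2 | +0.3 | sign changes |

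The last row shows that an intervention that saves money overall could be reported as adding cost. These values of H illustrate the range; they are not estimates.

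**Which pharmacist time is in the pool?**

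- For consultation time: the back-reference points to the one pharmacist-time cost already calculated. Training has its own later sentence, introduced as an addition. The same list includes consumables for measuring blood pressure, and section 3.6 has blood pressure monitored at each session, so the list is not confined to training.
- For training time: the list refers back to the sentence on training and equipment, and the sum names the consultation cost as something separate to be added.

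**The case against.** The strongest reply is that the section has two blocks. The first builds the consultation cost. The second deals with training and equipment, and the pharmacist time listed there is time spent in training, valued by the same method. The sum then adds the consultation cost to a pool that never contained it, giving C + F. This reading is possible, and the way the sum keeps the two parts separate supports it. It means that double counting cannot be called certain. It does not remove the problem: the text never says that the listed time is training time, and if it is, the later sentence on training costs leaves open whether that time is counted there again.

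A second reply is that a journal article condenses the costing, and itemised cost sheets belong elsewhere. That is fair for missing detail. Here, however, the article gives an explicit summation rule, and the objection is to what that rule says.

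A third is that the matter is secondary. Section 2.2 places cost-effectiveness after blood pressure control and adherence, and section 3.8 lists cost per HRQoL gained among the secondary outcomes. That stands: the primary blood pressure analysis is not affected.

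Some stronger inferences are tempting but not supported:

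- **That every ratio is inflated by 1 + s.** That factor applies to intervention cost. The ratios also contain H, and calling a ratio inflated presupposes a positive incremental effect.
- **That 30–60 minutes per patient would be charged as 60–120.** This takes only the two sessions of 15–30 minutes in section 3.6. Section 3.9 also costs a 12-month consultation, additional consultations and non-contact time.
- **That an equal split biases the ratios by charging non-attenders.** It changes how cost is spread over patients, but not the arm mean on which section 3.13 relies.

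**Conclusion.** The point holds as a conditional one. On its more natural reading, the summation rule in section 3.9 counts consultation time twice. If it is followed, per-patient intervention cost is overstated by C, a factor of 1 + s, which lies between 1 and 2. The incremental cost in every planned ratio rises by C per intervention patient. How much the ratios change in proportion cannot be derived from the article, because it gives neither unit costs nor the between-arm difference in other costs.

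The conclusion rests on reading the listed pharmacist time as consultation time. If it is training time and is counted once, there is no error in the sum, only unclear wording. The rule should be corrected before costs are analysed, since the literal version can only work against the intervention.

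**What to change.** Replace the summation sentence in section 3.9 with one that defines the two parts so that they do not overlap:

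- **Shared pool, divided equally among intervention participants:** non-consultation costs only. These are training (including any pharmacist time spent in training, counted once), equipment, materials, blood pressure consumables, and those telephone and administrative costs that are not recorded per patient. Telephone and administrative costs are listed for collection in section 3.7 and need a place in the sum.
- **Per-patient part:** the patient's own attended consultations times the cost per consultation. This is the only place where consultation time enters.

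Remove the unqualified entry for pharmacist time from the list of shared items, or rename it as pharmacist training time and cost it only under training. The change is one sentence plus one edited list entry. It needs no new data and does not touch the primary analysis.

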### 3.10. Data Management

All data will be confidentially stored in computers and entered manually in spreadsheets. Findings will be available to authorized individuals for analysis and reporting purposes only. To ensure the privacy and accuracy of the study data, the datasheets will be in a password-protected server, and data entry will be reconfirmed and double-checked for any potential errors during input. The research data will be published in a manner that ensures participants’ anonymity. A unique identifier will be used to coordinate participants’ data across baseline and all follow-up stages. Patients will be coded as numbers, with the code key stored in a password-protected document, ensuring all safety precautions. The patients who will complete all the scheduled follow-ups will be included in the analysis of results. To avoid a withdrawal bias, a strict intention-to-treat technique will be considered in our analysis. Furthermore, the variable imputation method will be used to handle the missing data. After each intervention, an interim analysis will be performed by the main investigator.

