### 3.8. Outcome Evaluation

The primary effectiveness of the outcome will be evaluated by changes in the SBP and DBP of the patients from baseline to final follow-up at 12 months post-intervention. The secondary outcome measures will include (1) BP controlled to target (SBP < 140 mmHg and DBP < 90 mmHg); (2) composite outcome of death (all-cause) or hospital admission due to CHD, heart failure, or stroke; (3) incremental cost per HRQoL gained from baseline to end of follow-up; (4) improvement in the knowledge of patients on healthy lifestyle; (5) change in dietary salt intake; (6) change in quality of life; (7) change in the prevalence of current smokers; and (8) the treatment adherence rate. Hypertensive patients with poor adherence to their treatment regimens experience uncontrolled blood pressure. Adherence to hypertension treatment is defined as following the treatment regimen agreed to with their physician. According to the previous literature [29,30,31], a reduction of 5 mmHg of SBP is considered clinically relevant as it has been found to be significantly associated with a risk reduction in CHD, stroke, and other serious cardiovascular events. Health service utilization parameters will include the number and reason for visits to physicians and hospital admission, and when further complicated, the death of the patient. The cost-effectiveness measures are incremental cost per mmHg BP reduction or cost per HRQoL gained from baseline to end of follow-up at 12 months. For determining dietary salt intake level, a 24 h urinary sodium measurement will be opted.

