## 5. Limitations

The main limitation could be the high dropout rate as patients may be too busy to attend an educational session, some might lose interest and discontinue during the study period, and some participants might miss their routine follow-up visits due to political unrest or any other unavoidable circumstance. Although the patients’ presence can never be guaranteed, the research team and the CP will try their best to contact and persuade patients to participate. Secondly, missing data can be an issue in this trial; however, the planned analyses will follow intent-to-treat methods to minimize bias from dropout over time. A repeated-measurement bias can also be expected as the same questionnaire will be used at both baseline and endline surveys. Finally, due to the short follow-up duration, the long-term benefits of this CP model may not be observed at length. Despite these limitations, the study findings can give a basis for improving the future care of hypertensive patients in primary healthcare facilities in South Asia.

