** *Outcome measurements (Control and intervention group)* **												
*Primary outcome*												
Change in SBP and DBP									x			x
*Secondary outcome*												
BP controlled to target									x			x
Composite outcome of death or hospital admission									x			x
Improvement in knowledge									x			x
Changes in lifestyle									x			x
Changes in drug adherence									x			x
HRQoL gained									x			x
Cost per unit of BP reduction									x			x
Cost per HRQoL gained									x			x

HRQoL, health-related quality of life; SBP, systolic blood pressure; DBP, diastolic blood pressure; BP, blood pressure.

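### Section 3.10 puts completers of all follow-ups into the analysis, which contradicts the intention-to-treat analysis stated there and in sections 3.13 and 5; if applied, it would exclude every death during follow-up

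*Protocol article*

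**What the plan says.** Protocol article, section 3.10 (Data Management), contains three consecutive statements on who is analysed and how gaps are handled:

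- The first names the analysis set: "The patients who will complete all the scheduled follow-ups will be included in the analysis of results".
- The second states a principle that points to a different set: "To avoid a withdrawal bias, a strict intention-to-treat technique will be considered in our analysis".
- The third deals with gaps in the data: "the variable imputation method will be used to handle the missing data".

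Section 3.13 (Statistical Analysis) opens with "All outcomes will be analyzed using the intention-to-treat principle". Section 5 (Limitations) warns that "The main limitation could be the high dropout rate as patients may be too busy to attend an educational session" and answers the resulting missing data by saying that "the planned analyses will follow intent-to-treat methods to minimize bias from dropout over time".

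Secondary outcome (2) in section 3.8 is the "composite outcome of death (all-cause) or hospital admission due to CHD, heart failure, or stroke". Table 2 schedules it for both arms at months 6 and 12. Section 3.13 also uses mortality, together with EQ-5D-5L, in the cost-effectiveness ratio for HRQoL.

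**The concern.** A set of patients who completed every follow-up and an intention-to-treat set are different populations. The article presents both as the analysis and ranks neither. Two analysts could each follow it faithfully and report different results for the primary outcome.

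Two things are at stake if the completer sentence is the one followed.

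- **Comparability of the arms.** Completion is observed after allocation. Section 3.6 and Table 2 give counselling sessions and phone calls to the intervention arm, while the control arm has usual pharmacy care. Attendance, and the kind of patient who keeps attending, can therefore differ by arm. Selecting on it can undo the balance that randomisation provides for blood pressure, control to target and adherence.
- **Deaths.** A patient who dies before the month-12 visit cannot have completed all follow-ups. The rule would remove exactly the patients who have one of the composite's events.

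**Working it through.** **1. The statements side by side.**

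| Place | Who is analysed |
|---|---|
| 3.10, completer sentence | patients with all follow-ups completed |
| 3.10, next sentence | strict intention-to-treat |
| 3.13 | intention-to-treat, all outcomes |
| 5 | intention-to-treat, as protection against dropout bias |

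The first row excludes any patient who misses a visit; the other three keep that patient. No section exempts an outcome from the completer sentence or calls completers a secondary set.

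**2. Deaths under the completer sentence.** Death before month 12 means the last follow-up is missed, so the completer set holds 0 deaths at any death rate. Admissions in patients who later die or stop attending are lost as well. The documents give no event rates. As an illustration on assumed 12-month risks:

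| Death | First event by admission | Deaths among 3600 | Deaths as share of composite events |
|---|---|---|---|
| 1% | 3% | 36 | 0.01/0.04 = 25% |
| 2% | 5% | 72 | 0.02/0.07 = 29% |
| 3% | 5% | 108 | 0.03/0.08 = 38% |

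For example, an assumed 3% against 2% mortality between arms is a difference of 1 percentage point by intention-to-treat. Among completers the difference in deaths is 0 by construction.

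**3. Bias in systolic pressure.** In one arm, let p be the dropout fraction and g the mean change in dropouts minus that in completers. The full-arm mean is the completer mean plus p x g, so the completer mean is off by p x g. The treatment difference is off by the difference between arms in p x g. With assumed values:

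- Both arms 20% and 5 mmHg: 0.20 x 5 - 0.20 x 5 = 0.
- 20% and 5 mmHg in one arm, no gap in the other: 0.20 x 5 = 1.0 mmHg.
- 30% and 8 mmHg in one arm, no gap in the other: 0.30 x 8 = 2.4 mmHg.

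Section 3.8 treats 5 mmHg systolic as the relevant reduction, so the last two are 1.0/5 = 20% and 2.4/5 = 48% of it. The direction depends on which arm has the gap.

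**4. Room for losses in the sample size.** Section 3.1 gives an effect of 4.65, an SD of 49.78, 80% power and 5% significance; section 3.13 makes tests two-tailed. Per arm, 2 x (1.960 + 0.842)² x 49.78² / 4.65² rounds up to 1800, or 3600 in total. This is the stated figure, with no allowance for dropout. Under the same unclustered formula, completer analyses at assumed losses give:

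| Loss | Patients kept | Power |
|---|---|---|
| 5% | 3420 | 78% |
| 10% | 3240 | 76% |
| 20% | 2880 | 71% |
| 30% | 2520 | 65% |

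Part of this loss would occur under any analysis, because missing month-12 readings stay missing. The completer rule adds to it by also discarding patients who have a month-12 reading but missed another visit.

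**The case against.** The strongest reply is that one sentence in a data-management section should not be read as the governing rule. It lacks the word *only*. The sentence after it states an aim that points the other way, the dedicated analysis section is firm on intention-to-treat, and the limitations section repeats it. The plan also shows that deaths are meant to count: Table 2 schedules the composite in both arms, mortality enters the HRQoL ratio, and one hospital-stay ratio is expressly confined to patients still alive, which would be redundant if everyone analysed had survived.

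Much of this stands. A reader might infer that the plan has settled on completers and that all deaths will be lost. The documents do not support that, because the loss follows only if the completer sentence overrides section 3.13. What does not stand is the idea that the sentence is harmless. Saying who enters the analysis reads naturally as a restriction, and the sentence has no other evident purpose.

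A reader might also infer that a completer set leaves nothing to impute, so that imputation is a further contradiction. That goes too far. Patients who attend every visit can still have gaps in single items, and section 3.14 lets them decline any question. The conflict is between completers and intention-to-treat.

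Finally, the documents give no dropout rate, no difference between arms and no gap, so a bias of 1.0 or 2.4 mmHg is not a prediction. It needs the arms to differ, and zero belongs in the range.

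**Conclusion.** The completer sentence is wrong as written. It contradicts the sentence that follows it, section 3.13 and section 5, and it leaves the primary analysis set undetermined.

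The consequences are conditional on that sentence being applied. In that case every death before month 12 leaves the analysis and the death component of secondary outcome (2) cannot be estimated, which follows by logic and needs no assumed rate. The systolic bias would range from 0 (arms alike) to 1.0 or 2.4 mmHg on the assumed one-arm values. If section 3.13 is followed instead, neither consequence arises and the defect is one of wording. Because the choice decides who enters the primary comparison, it should be settled before any outcome data are analysed.

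**What to change.** - Delete the completer sentence in section 3.10, or reword it so that completers form a sensitivity set only.
- State that the primary set is every enrolled patient, analysed by the allocation of the patient's pharmacy, using all available month-6 and month-12 blood pressure in the mixed model that section 3.13 already plans, with no requirement to attend every visit.
- State that deaths and qualifying admissions count as composite events for all enrolled patients regardless of attendance, and that the mortality input to the HRQoL ratio uses the same patients.

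The first two are wording changes. The third may need follow-up calls to patients who stop attending; section 3.2 already collects at least two contact numbers for each, so the extra effort is small. Detailed tracing procedures can be left to the full protocol or analysis plan.
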